##### 2.2.3.3 Recruitment

A total of 105 clinical nurses from the participating centers will be recruited and trained. From the previously selected sample, each nurse will invite 10 candidates from their health center to participate (seven unexposed and three exposed), after ensuring that they meet the inclusion and exclusion criteria.

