##### 2.2.3.2 Sample size

Based on the assumption of a proportional hazards model for survival times, the sample size was estimated to allow the comparison of two curves. The probability of a change in functionality of < 5 points at 18 months was previously estimated to be 47% in the unexposed group (22) and this figure was considered to decrease by at least 10% in exposed patients. Considering a ratio of 2:1 between the sample sizes of the unexposed and exposed groups, for a CI of 95%, a power of 80%, and a dropout rate of 20%, the sample size was calculated to be 1,035 subjects (690 unexposed and 345 exposed). A randomized sampling by quotas for the included health centers in each of the regions will be performed.

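### The recruitment quota yields at most 315 exposed participants, against the 345 that the sample size calculation requires

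*Protocol article*

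**What the plan says.** All of this concerns the cohort study with 18 months of follow-up (section 2.2.3 of the protocol article).

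- **Target (2.2.3.2 Sample size).** The calculation compares two survival curves under proportional hazards. The probability of a change in functionality below 5 points at 18 months "was previously estimated to be 47% in the unexposed group", and "this figure was considered to decrease by at least 10% in exposed patients". The allocation is fixed: "Considering a ratio of 2:1 between the sample sizes of the unexposed and exposed groups". The remaining inputs are given as "for a CI of 95%, a power of 80%, and a dropout rate of 20" per cent. The result: "the sample size was calculated to be 1,035 subjects (690 unexposed and 345 exposed").
- **Recruitment rule (2.2.3.3 Recruitment).** "A total of 105 clinical nurses from the participating centers will be recruited and trained", and "each nurse will invite 10 candidates from their health center to participate (seven unexposed and three exposed"). Invitations go to people from a sample drawn beforehand, once their eligibility has been checked.
- **Consent (2.2.3.1 Population).** Written consent is a condition of entry. The article gives no expected acceptance rate.

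**The concern.** The two adjacent sections fix different group sizes. The overall total hides this: 1,050 invitations look sufficient for 1,035 participants, but the surplus is all in the unexposed group and the deficit all in the exposed group. The exposed group is the smaller one and therefore limits the precision of the comparison between infected and uninfected people, which is the study's second specific aim.

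The quota is also expressed as people invited. The 20% dropout allowance is already used up inside the 1,035, so it cannot also absorb people who decline at the outset. Taken literally, the rule has no margin for refusals among the exposed.

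**Working it through.** **Inputs.** From 2.2.3.2: 47% in the unexposed, a decrease of 10% in the exposed, 2:1 allocation, 95% confidence, 80% power, 20% dropout. From 2.2.3.3: 105 nurses, 7 unexposed and 3 exposed each. Inferred, because the article does not state them: a two-sided test, the Schoenfeld events formula, and dropout applied by dividing by 0.8.

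**1. Reproduce 1,035.** Take 47% and 37% as the proportions without the event at 18 months.

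- Hazard ratio = ln(0.37)/ln(0.47) = 1.317, so (ln HR)² = 0.0758.
- Events = (1.960 + 0.842)² / [(1/3)(2/3)(ln HR)²] = 7.849 / (0.2222 × 0.0758) = 466.2.
- Mean event probability = (2 × 0.53 + 0.63)/3 = 0.563.
- Evaluable participants = 466.2/0.563 = 827.6.
- Enrolled = 827.6/0.8 = 1,034.5, which matches 1,035 (690 + 345).

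The match shows that dropout is already included and that the 10% was used as 10 percentage points. A one-sided test gives 815. Reading the 10% as relative (47% to 42.3%, HR 1.140) gives about 4,742.

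**2. Multiply out the quota.**

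| | Target | Quota (105 nurses) | Difference |
|---|---|---|---|
| Unexposed | 690 | 105 × 7 = 735 | +45 |
| Exposed | 345 | 105 × 3 = 315 | −30 |
| Total | 1,035 | 1,050 | +15 |
| Ratio | 2:1 | 2.33:1 | |

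The exposed shortfall is 30/345 = 8.7%. The overall margin for refusal is 15/1,050 = 1.4%. Among the unexposed it is 45/735 = 6.1%, and among the exposed there is none.

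**3. Power under the same formula.** Power = Φ(√[D·p(1−p)]·ln HR − 1.960), where D is the number of events after 20% dropout and p is the exposed share.

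- Target 690/345 (evaluable 552/276): D = 552 × 0.53 + 276 × 0.63 = 466.4; p(1−p) = 0.2222; power 80.0%.
- Quota 735/315 (evaluable 588/252): D = 588 × 0.53 + 252 × 0.63 = 470.4; p(1−p) = 0.21; power 78.1%.

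D rises slightly under the quota because more people are recruited in total. The less favourable split outweighs that, for a net loss of about 2 points.

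**4. Effect of refusals that are not replaced.** The acceptance rate is an assumption, taken as equal in both groups. D shrinks in proportion.

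| Assumed acceptance | Power |
|---|---|
| 100% | 78.1% |
| 95% | 76.0% |
| 90% | 73.7% |
| 80% | 68.7% |
| 70% | 62.9% |

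**5. Check a quota that reaches the target.** With 75 nurses at 7+3 and 30 at 6+4, exposed = 225 + 120 = 345 and unexposed = 525 + 180 = 705, total 1,050. Evaluable 564/276: D = 472.8, p(1−p) = 0.2206, power about 80.3%.

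**The case against.** The best defence is that the documented gap is small. Seven and three is the nearest whole-number version of 2:1 with ten people per nurse, and the cost is about 2 points of power. That is correct and sets the severity. It does not remove the contradiction: even if inviting is read as enrolling, 105 nurses at three each cannot exceed 315 exposed.

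A second defence is that refusals may well be replaced. Nurses draw from a sample selected beforehand, which may be larger than the ten invited. The sample size section speaks of sampling by quotas, and quotas are normally filled. A total of 1,050, just above 1,035, also suggests that ten participants per nurse was the intention. A replacement procedure is a detail that a journal article commonly leaves to the full protocol, so its absence is not counted as a fault here. This defence stands as far as it goes. If decliners are replaced, only the 30-person shortfall and the 2-point loss remain.

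Two stronger conclusions are tempting, and the document supports neither:

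- **That power falls well below 80%, into the 60s or lower.** This needs both an acceptance rate and a no-replacement rule, and the article states neither.
- **That power is really far lower because the 10% decrease is relative.** The article's own 1,035 rules that reading out. Only the 10-point reading reproduces it, so this is a matter of wording and not a power defect.

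**Conclusion.** The point holds as a contradiction between sections 2.2.3.2 and 2.2.3.3. The quota delivers at most 315 of the 345 exposed participants, at 2.33:1 instead of 2:1, whatever the acceptance.

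With full acceptance and 20% dropout, power is about 78.1% instead of 80%. This rests on the inferred two-sided Schoenfeld calculation, which reproduces the stated sample size. Any further loss is conditional on refusals that are not replaced, and the figures for it illustrate assumed acceptance rates only.

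Severity is moderate. The stated size is not what the stated rule produces, but the consequence that can be shown from the document alone is small and cheap to correct.

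**What to change.** 1. **Restate the quota as a number enrolled.** Say that people who decline are replaced from the sample already drawn for that centre. Eligibility needs no new rule, because it is checked before invitation.
2. **Set the quota to reach 345 exposed.** One option is 75 nurses at 7+3 and 30 nurses at 6+4, which keeps 105 nurses and 1,050 participants. The allocation of the 6+4 nurses should be checked against the quotas for centres within each region. The cost is some extra invitations and an uneven load across nurses, with no extra staff.
3. **If recruitment can no longer be changed, restate the target.** Section 2.2.3.5 describes training and data collection materials partly in the past tense, so fieldwork may have begun. In that case give the target as 735 unexposed and 315 exposed, with about 78% power at full acceptance, and state the acceptance expected or observed. This costs only wording.
4. **Minor clarification in 2.2.3.2.** Write the effect as a decrease of 10 percentage points (47% to 37%, hazard ratio about 1.32).

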##### 2.2.3.4 Variables

The exposure variable will be SARS-CoV-2 infection confirmed by diagnostic testing between May 11th of 2020 and the recruitment start date. The outcome variables will be mortality, functionality (Barthel scale), quality of life (EuroQol-5D), mental health (Hamilton depression rating scale), cognitive capacity (Mini-Mental State Examination), and frailty (Frailty index). In addition, sociodemographic (age and gender) and clinical, infection-related, and pandemic-context variables will be recorded. The date of the infection diagnosis and length of hospitalization will also be recorded for the cohort of exposed patients, as well as diagnoses of infection during the follow-up for the cohort of unexposed patients.

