## 1 Introduction

The coronavirus disease 2019 (COVID-19) has caused a significant social and economic impact worldwide since the appearance of the first cases in the city of Wuhan (China) (1). The pandemic forced public health authorities to impose drastic measures as an epidemiological containment strategy. The Spanish government decreed a state of alarm across the national territory on March 14, 2020, which limited the free movement of citizens to essential acts and ordered home confinement for the population. In other countries, in addition to these measures, public transportation was shut down (2). Ninety-eight days later, on June 21, the state of alarm came to an end.

On a worldwide level, containment measures to reduce disease transmission were effective, especially home confinement (3), although they also entailed a substantial social impact (4) and a negative effect on physical activity levels, sleep quality, and wellbeing (5). These unprecedented measures, along with the rapid and unpredictable evolution of the pandemic, caused natural responses of fear, stress, anxiety, and loneliness among the population (6). Furthermore, the self-care and health management in people suffering from multiple comorbidities and preexisting mental disorders were adversely affected by the subsequent difficulties in accessing social-health services (7).

Numerous studies have analyzed the impact of the COVID-19 pandemic and the adopted preventive measures on the population. The social-distancing regulations imposed in all countries to control the pandemic have brought significant psychosocial consequences for individuals (8, 9).

This impact has been especially noteworthy in vulnerable groups such as children, migrants, people at risk of exclusion, individuals with psychiatric pathology, the older adults, and caregivers (8). The lock-down has been specially difficult to the older adults people, in terms of shielding and self-isolation. The lack of social communication and community networking could have affected the older adults's mental health, as well as the engagement with their own health needs and management (10).

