#### 2.2.3 Cohort study with a follow-up of 18 months

##### 2.2.3.1 Population

Based on the population of the prospective study, the participants will be ≥75 years of age, with at least one record in the last half of 2019 and another one in the first half of 2022, will not be institutionalized, and must provide informed written consent. Subjects with sensory deficits, cognitive impairment, a Barthel ADL index ≤ 5 points, life expectancy ≤ 9 months, or participants transferred during the recruitment period will be excluded.

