##### 2.2.3.6 Analysis

Population characteristics will be described with their relevant 95% CI. The baseline characteristics will be compared between both groups upon enrolment. Kaplan-Meier survival curves will be generated for the main variables, which will be compared using the log-rank test. Cox models will be generated to study the impact of infection on the outcome variables at 6, 12, and 18 months and to adjust for sociodemographic and clinical characteristics of interest.

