The analysis of real-life data, obtained from a cohort from 11 Spanish regions representative of the peninsular and insular population, rural and urban setting, will favor the external validity of the results and allow their extrapolation to similar contexts. These data will be of great epidemiological value, as the estimated study population exceeds 1.5 million primary care users and the information will be collected in routine clinical practice, including nursing diagnoses. In addition, the collected data will allow observing the changes in the demand for health resources, occurred during and after the pandemic, based on the information automatically generated by the system (e.g., number and types of consultations). By following up two cohorts over 18 months, this study aims to explore if there have been changes in the aging process of the included population and whether these may be due to the biological impact of the disease, or the situation experienced during the pandemic.

One strength of this study to highlight is the robustness of the outcome variables, which are mostly self-reported outcomes or from EMRs and SNLs registries. The enrolment and follow-up of participants will be conducted by their assigned primary care nurses, which will minimize dropouts and increase the quality of records. In order to avoid selection bias, the cohort of subjects exposed to COVID-19 will only include those individuals diagnosed after May 11th of 2020, as that was the time point at which the diagnosis required confirmatory testing in Spain.

The qualitative methodology uses interviews and focus groups to provide a vision of the reality experienced by the study population. This approach will allow understanding and interpreting the social, political, and economic dimensions associated with the use of health services by patients and caregivers.

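### Study 2 defines exposure by a confirmed test but states no infection-free criterion for the unexposed, so known unconfirmed infections fall in the comparator and exposure partly reflects contact with services

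*Protocol article*

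**What the plan says.** Section 2.2.3.4 (Variables) of the protocol article gives the exposure rule: "The exposure variable will be SARS-CoV-2 infection confirmed by diagnostic testing between May 11th of 2020 and the recruitment start date". The unexposed group has no definition of its own. The places where one might be expected say this:

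- **Section 2.2.3.1 (Population):** participants in both groups must be people "with at least one record in the last half of 2019 and another one in the first half of 2022". No negative test and no history free of infection is asked for.
- **Section 2.2.3.3 (Recruitment):** "each nurse will invite 10 candidates from their health center to participate (seven unexposed and three exposed"), once the inclusion and exclusion criteria have been checked.
- **Section 2.2.3.4:** infection among the unexposed is named only prospectively, "as well as diagnoses of infection during the follow-up for the cohort of unexposed patients". Unspecified infection-related and pandemic-context variables are also to be recorded.
- **Section 2.2.3.6 (Analysis):** the Cox models are "to adjust for sociodemographic and clinical characteristics of interest". Testing and use of services are not named.
- **Section 3 (Discussion):** to avoid selection bias, "the cohort of subjects exposed to COVID-19 will only include those individuals diagnosed after May 11th of 2020", because confirmatory testing was required from that date.
- **Section 3.1 (Limitations):** record quality and survival bias appear; exposure misclassification does not.

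**The concern.** Read literally, the rule makes exposed mean both infected and confirmed by a test. Everyone else who is eligible can be invited as unexposed, including people who know they were infected inside the window but whose infection was never laboratory-confirmed. The safeguard in the Discussion works on one side only. It keeps unconfirmed cases out of the exposed group and does nothing about them in the comparator.

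Two distortions of the main contrast follow.

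- **Dilution.** Infected people in the comparator pull the hazard ratio toward 1 and reduce power.
- **Selection by contact.** A confirmed test usually requires contact with services, through symptoms, contact tracing or admission. If people with more contact or more illness also decline faster, the hazard ratio moves away from 1.

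This matters for the stated purpose. The Discussion wants the two cohorts to help separate the biological effect of the disease from the circumstances of the pandemic. An exposure variable that partly records contact with services blurs that separation.

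**Working it through.** **1. Inputs from section 2.2.3.2 (Sample size).** Probability of remaining free of the functional event at 18 months: 0.47 in the unexposed, 10 points lower (0.37) in the exposed. Allocation is 2:1, the confidence level 95% (taken as two-sided 5%), power 80%, dropout 20%, total 1,035 (690 and 345). The absolute reading of the 10% decrease is used because it reproduces the stated total; a relative 10% decrease would need about 4,700.

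**2. Reproducing the plan's figure (Schoenfeld).**

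- HR = ln(0.37)/ln(0.47) = 1.317, so ln HR = 0.2752.
- Events = (1.960 + 0.842)² / [(1/3)(2/3)(0.2752)²] = 466.2, rounded up to 467.
- Mean event probability = (2 × 0.53 + 0.63)/3 = 0.563.
- N = 467/0.563 = 829, and 829/0.80 = 1,036, against 1,035 stated.

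The plan's arithmetic is sound. It takes the comparator to be infection-free.

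**3. Dilution.** Let q be the share of the unexposed with an unconfirmed infection. The documents give no value, so q is an assumption. Suppose first that such infections have the full effect of confirmed ones. Then

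- S_u = (1 − q) × 0.47 + q × 0.37
- HR = ln(0.37)/ln(S_u)
- events D = 828 × [2(1 − S_u) + 0.63]/3, where 828 = 1,035 × 0.80
- power = Φ(√(D × 2/9) × ln HR − 1.960)

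| q (assumed) | S_u | HR | Events | Power |
|---|---|---|---|---|
| 0% | 0.47 | 1.32 | 466 | 80% |
| 10% | 0.46 | 1.28 | 472 | 72% |
| 20% | 0.45 | 1.25 | 478 | 62% |
| 30% | 0.44 | 1.21 | 483 | 51% |

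**4. If unconfirmed cases are milder.** Give them half the effect, an event-free probability of 0.42. At q = 20%, S_u = 0.8 × 0.47 + 0.2 × 0.42 = 0.46, which is the 10% row: 72% power, not 62%. At q = 10%, S_u = 0.465 and power is 76%; at q = 30%, S_u = 0.455 and power is 67%. The table therefore gives the largest loss at each share if unconfirmed infection is milder.

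**5. The opposite direction.** Suppose frequent attenders make up a share p_e of the exposed and p_u of the unexposed, and decline at h times the rate of others. The observed hazard ratio is then multiplied by roughly [1 + p_e(h − 1)]/[1 + p_u(h − 1)]. With p_u = 0.35 (all values assumed):

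- p_e = 0.50, h = 1.5: 1.25/1.175 = 1.06
- p_e = 0.60, h = 2.0: 1.60/1.35 = 1.19

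This inflation of 6% to 19% would act against the dilution in step 3. Nothing in the documents says which is larger.

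**The case against.** The article condenses a fuller protocol, and much can be said in its defence.

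- **Silence is not absence.** A reader might infer that nobody is asked about an untested or home-tested infection. The documents do not support that. The infection-related and pandemic-context variables are unspecified, the data collection notebook is not shown, and the full protocol may define the unexposed more tightly. What stands is narrower: the exposure rule is stated, and applied as written it leaves a known unconfirmed infection in the comparator even if that infection is recorded elsewhere.
- **Access to testing.** A reader might infer that tests were hard to obtain in the window. The Introduction says that self-care and health management "were adversely affected by the subsequent difficulties in accessing social-health services", but this is background on people with comorbidities and mental disorders and does not mention testing. The overwhelmed health system it describes belongs to the first weeks, before 11 May 2020. The link between testing and contact follows from the design; the documents do not demonstrate it.
- **Partial safeguard.** Requiring a record in late 2019 and in early 2022 removes people with no recorded contact in either period, in both groups. This narrows the difference in contact but does not equalise testing.
- **Magnitude.** The shares are assumed, full effect in unconfirmed cases is pessimistic, and the plan's 10% is a minimum effect, so a larger true effect would leave reserve. These objections all stand. The power figures are illustrations, not estimates.
- **Covariates and sensitivity analyses** are commonly left to an SAP. That is fair as regards their absence, which is not the fault here. The fault is the group definition, which the article does fix.

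**Conclusion.** The point holds as a weakness in how the comparison groups are defined. The exposed are defined by a confirmed test, the article states no infection-free criterion for the unexposed, and the safeguard in the Discussion protects only the exposed side. Known but unconfirmed infections therefore fall in the comparator, and exposure partly reflects contact with services.

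The size is not known. If 10% to 30% of the unexposed carried the full effect of confirmed infection, power would be about 72% to 51%, with higher figures if unconfirmed cases are milder. This rests on assumed shares, the absolute reading of the 10% decrease, and proportional hazards.

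Two stronger conclusions are tempting and unsupported. One is that the study is underpowered: the documents give no contamination share. The other is that the hazard ratio will be biased in a particular direction: the two mechanisms oppose each other and no net effect is shown. The contrast remains estimable, but it cannot be read cleanly as the effect of infection. This is a worthwhile and inexpensive improvement; it does not invalidate the design.

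**What to change.** 1. **Define the unexposed explicitly.** At baseline, or at the next scheduled visit if enrolment has begun, ask about any positive home test or clinician-diagnosed COVID-19 without laboratory confirmation in the window. Analyse those who report one as a separate probable-infection group, not as unexposed.
2. **Adjust for prior contact.** Link each participant's 2019 primary care contact count from the Study 1 records and name it in the Cox adjustment set. Sections 2.2.2.3 and 2.2.2.4 already plan to extract use of health services for 2018–2023, and a 2019 count cannot be a consequence of infection.
3. **Add one sensitivity analysis.** Limit the unexposed to people with at least one negative test in the window and no reported positive. Keep it as a sensitivity analysis only: being tested is itself selective, and one negative test does not exclude infection at another time.
4. **Extend the Limitations** (section 3.1) to say that asymptomatic, untested infections remain in the comparator.

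**Cost.** A few REDCap items, a linkage to the Study 1 records (with test results for item 3), and one further analysis; no serology and no extra visit. The answers rely on recall. The comparator shrinks: shares of 10% to 30% would be 69 to 207 of 690. Even so, in the best case where all such infections are identified and moved, the 552 evaluable unexposed (690 × 0.80) become 497 or 386 against 276 exposed. Events are then 497 × 0.53 + 276 × 0.63 = 437, or 386 × 0.53 + 276 × 0.63 = 379. The same formula with HR 1.317 and exposed fractions of 0.357 and 0.417 gives power of about 79% and 75%. Under the step 3 assumptions, leaving them in gives 72% and 51%. Recall will find only some of these infections, so the real gain lies in between.
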